### Analysis of Primary Endpoint(s)

The primary endpoint, the per-voxel remyelination/demyelination count changes in NABT at 12 and 24 weeks will be summarized for each group with descriptive statistics: mean, standard deviation, median, minimum and maximum and a two-sided 95% confidence interval. For testing differences in remyelination/demyelination between groups, an analysis of covariance (ANCOVA) on the ranked data with effects for treatment group (RRMS vs. HC), treatment period (1st 3 months vs. 2nd 3 months), age, and gender will be performed. Model assumptions of linearity, normality and homoschedasticity will be verified. For testing differences across time (at week 12 and 24) within the RRMS treatment group, the Wilcoxon signed rank test will be used.

Exploratory analyses on the primary endpoint may be performed to include other covariates of interest, such as time since MS diagnosis, immune status, etc.

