| **Statistical methods (includes sample size calculation)** | Sample size is based on clinical rather than statistical considerations.  All statistical tests will be two-tailed and considered significant at the α=0.05 level of significance.  T-tests and chi-square tests for independent samples will be used for comparison of demographic and clinical characteristics between RRMS patients and HC. For testing differences across groups, an analysis of covariance (ANCOVA) on the ranked data with effects for treatment group (RRMS vs. HC), treatment period (1st 3 months vs. 2nd 3 months), age, and gender will be performed. Model assumptions of linearity, normality and homoschedasticity will be verified. For testing differences across time (at week 12 and 24) within the RRMS treatment group, the Wilcoxon signed rank test will be used.  VW-MTR spatial distribution analysis will be conducted directly on the images. Similarly, voxel-wise SWI spatial distribution analysis will be conducted directly on the images.  Analysis of MRI measures may require a variance stabilizing transformation, if skewness is observed in their assessments. Each of the MRI parameters will be examined and appropriate transformations will be applied, if necessary. |

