### Primary and Secondary Endpoints

Primary Endpoint

The primary endpoints are the numbers of voxels (counted in milliliters) that change in VW-MTR value (both increase and decrease) from baseline to six-months in NABT of RRMS subjects treated with Rebif® as compared to NABT of HC.

Secondary Endpoints

The secondary MRI endpoints for RRMS subjects treated with Rebif® are:

- the number of voxels that increase in VW-MTR value at three months vs. baseline in NABT
- the increase and decrease in number of voxels from VW-MTR at three- and six-months vs. baseline in lesions
- brain volume using 3D-T1 imaging at three- and six-months vs. baseline in whole brain and GM
- the amount of iron deposition identified via SWI at three- and six-months vs. baseline in DGM, NABT and lesions
- lesion volume from T2-LV, T1-LV and T1-Gd-LV imaging at three- and six-months vs. baseline

The secondary immunology endpoints for RRMS subjects treated with Rebif® (six-months vs. baseline) are:

*Flow cytometry studies on CD4+ and CD8+ gated T-Cells:*

- intracellular IFN-gamma, IL-4, IL-17A, IL-17F, IL-21, IL-22 and IL-10 production
- nerve growth factor (NGF) and brain derived neurotropic factor (BDNF) secretion

*RT-PCR studies on:*

- Magnetic beads separated CD14+ monocytes
  - TLR3, 7 and 9;
  - cytokines IL-1α, IL-1β, IL-23p19, TGF-β, IL-12p70, IL-10, IL-27p28
  - cytokine receptors IL-1R1, IL-12Rβ, IL-23R, IL-21R, and IL-27R.
- Magnetic beads separated CD4+ and CD8+ T-cells
  - transcription factors T-bet, GATA3, ROR, IRF4 and FoxP3;
  - cytokines IFN-gamma, IL-4, IL-17A, IL-17F, IL-21, IL-22 and IL-10;
  - cytokine receptors IL-1R1, IL-23R, IL-21R, IL-12Rβ and IL-27R,
  - neurotrophic factors NGF and BDNF

Other secondary endpoints of the study examine potential associations of the effects of Rebif® in the CNS with peripheral effects on:

- number of clinical relapses
- time to first clinical relapse
- immune cell phenotype: related to CNS infiltration (Th17 cells)
- immune cell production of neurotrophic factors: related to remyelination or preservation of gray matter volume, and
- ferritin and transferrin levels: potentially associated with levels of CNS iron deposition.

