## Description of Statistical Analyses

### General Considerations

All statistical tests will be two-tailed and considered significant at an α=0.05 level of significance; all confidence intervals will be two-sided 95% confidence intervals.

Dropouts, if any, will be examined. Subjects who stop the Medicinal Product will be asked to remain in the study and will be analyzed with the intention to treat, but adding a covariate that alternative therapies have been given. Individual data will be analyzed. No imputation of missing data will be performed.

T-tests and chi-square tests for independent samples will be used for comparison of demographic and clinical characteristics between RRMS patients and HC.

VW-MTR and SWI spatial distribution analysis will be conducted directly on the images. Analysis of MRI measures may require a variance stabilizing transformation, if skewness is observed in their assessments. Each of the MRI parameters will be examined and appropriate transformations will be applied, if necessary.

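### The primary endpoint is the baseline-to-six-month change, but the only RRMS-versus-control test pools two periods and does not isolate it

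*Protocol*

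**What the plan says.** Section 5.1.2 (Primary and Secondary Endpoints), with the same text in the Synopsis, gives one time frame and one comparison: "The primary endpoints are the numbers of voxels (counted in milliliters) that change in VW-MTR value (both increase and decrease) from baseline to six-months", with the RRMS patients set against healthy controls. The same section lists as a secondary endpoint "the number of voxels that increase in VW-MTR value at three months vs. baseline in NABT".

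Section 8.4.2 (Analysis of Primary Endpoint(s)) restates the endpoint as "The primary endpoint, the per-voxel remyelination/demyelination count changes in NABT at 12 and 24 weeks". It plans three things:

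- descriptive statistics by group, with a 95% confidence interval;
- an ANCOVA on ranks "with effects for treatment group (RRMS vs. HC), treatment period (1st 3 months vs. 2nd 3 months), age, and gender will be performed", which is the only comparison of RRMS with controls (the statistical methods row of the Synopsis has the same model);
- a within-patient test: "For testing differences across time (at week 12 and 24) within the RRMS treatment group, the Wilcoxon signed rank test will be used".

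No group-by-period term is listed. Section 8.4.3 says that the secondary endpoints are to be tested in a similar way and leaves further details to a statistical analysis plan.

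**The concern.** A single baseline-to-six-month value per subject cannot carry a factor with two period levels. The model in Section 8.4.2 must therefore be fitted to something other than the endpoint in Section 5.1.2, or to that endpoint together with something else. The p-value reported as primary would then not belong to the stated primary endpoint. Depending on when the groups diverge, the test could miss a real six-month difference, or reject when there is none at six months. The two statements are both already fixed in the protocol, so an analysis plan that followed one would contradict the other.

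**Working it through.** The protocol states no power, effect size or standard deviation (Section 8.1), so there is no figure of its own to reproduce. The check compares the texts and then illustrates the consequence.

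**1. What the group effect estimates.** With both rows present for every subject, and age and gender constant within subject, write the model on the joint ranks as

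rank = intercept + γ·group + π·period + β₁·age + β₂·gender + error.

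The least-squares estimate is γ = (D₁ + D₂)/2, where D₁ and D₂ are the adjusted group differences in the two rows. It equals D₂ only if D₁ = D₂. The protocol does not use the word average; it follows from the listed main effects.

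**2. Two readings of the rows.**

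| Reading | Row 1 | Row 2 | Where the six-month volume stands |
|---|---|---|---|
| Successive intervals (literal sense of the period factor) | months 0–3 | months 3–6 | not in the model; months 3–6 are not an endpoint in Section 5.1.2 |
| Cumulative changes (suggested by the 12- and 24-week phrase) | weeks 0–12 | weeks 0–24 | one row of two, pooled with the 12-week change |

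**3. Successive intervals cannot reproduce the six-month volume.** The MRI Analysis section classifies each voxel on a pairwise difference map as changing or not, and then sums the volume. Such volumes do not add. Toy figures: 10 mL rises in months 0–3, 4 mL of other voxels rises in months 3–6, and r mL of the first 10 reverts.

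- Mean of the periods: (10 + 4)/2 = 7 mL, whatever r is.
- Volume rising over 0–6 months: 10 − r + 4 = 14, 9 or 4 mL for r = 0, 5 or 10.

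**4. Effect of pooling under the cumulative reading.** Simulation with 25 RRMS and 15 controls (Section 5.1.4) and 4,000 runs per scenario. Assumed, not from the documents: log-normal volumes, group differences in SD on the log scale, within-subject correlation 0.5, age uniform over 18–65 and gender at random. The pooled test uses each subject's mean rank, so that the comparison concerns what is tested and not how repeated rows are handled. The Week 24 test is a rank ANCOVA on row 2 alone. Both are adjusted for age and gender, two-sided at 0.05.

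| Difference in row 1, row 2 (SD) | Pooled test rejects | Week 24 test rejects |
|---|---|---|
| 0, 0 | 4.7% | 5.2% |
| 0, 1 | 39% | 82% |
| 0.5, 1 | 69% | 80% |
| 1, 1 | 91% | 82% |
| 1, 0 | 39% | 5% |

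Monte Carlo standard error near 39%: √(0.39 × 0.61/4000) ≈ 0.8 percentage points.

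**The case against.** The strongest reply is that the six-month change is not absent from the plan. On the cumulative reading it is one of the two modelled rows. It is summarised by group with a confidence interval, and it may enter the signed rank test within RRMS. That stands. A reader might infer that the endpoint is never analysed, and the text does not support that. But none of these is a test of RRMS against controls on the six-month change alone.

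A second reply is that pooling can help. That stands too: with equal differences in both rows the pooled test rejects more often (91% against 82%). The fault is a mismatch between endpoint and test, not a one-way loss of power.

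A third is that this is a non-randomised pilot meant to characterise an effect, with details left to an analysis plan. That limits what the p-value can carry, but deferral of details does not settle two conflicting protocol statements.

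Four stronger inferences are tempting and are not supported:

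- **Short-interval maps miss most slow change.** A simple per-voxel threshold calculation would suggest this, but the pipeline uses threshold-free cluster enhancement with Monte Carlo inference, which such a calculation does not model.
- **Dose titration dilutes the first period.** The titration weeks lie inside the baseline-to-Week-24 interval as well, and nothing in the protocol links dose delivered to voxel volume.
- **Two primary directions inflate the error rate by a known amount.** Section 8.4.1 does say "All statistical tests will be two-tailed and considered significant at an α=0.05 level of significance", but a rule for combining two directions is commonly left to the analysis plan. Both volumes come from the same map, so independence cannot be assumed.
- **The increase-only three-month endpoint makes a positive result easier.** It is prespecified, secondary and tested two-sided, and naming one direction means fewer tests. Section 8.4.2 also summarises both directions at 12 weeks. At most it is an asymmetry of wording.

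**Conclusion.** The point holds in this form: the protocol gives the primary endpoint two time frames, and the only between-group test does not isolate the baseline-to-six-month change on either reading of the period rows. That conclusion rests on the text alone. It should be corrected, because the model as written yields a primary p-value for a different quantity.

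The size depends on when the groups diverge. The simulated figures range from a large loss (39% against 82%) through a modest gain (91% against 82%) to rejection well above the nominal level when there is no six-month difference (39% against 5%). They rest on the assumed distribution, effect sizes and correlation, and they apply to the cumulative reading. For successive intervals the toy volumes show only that the six-month figure cannot be recovered; they do not estimate how far off it would be in this trial.

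**What to change.** In Section 8.4.2 and the statistical methods row of the Synopsis:

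- Define the primary endpoint as in Section 5.1.2, and name as the primary test the RRMS-versus-control contrast on the baseline-to-Week-24 difference map, separately for increase and for decrease.
- Specify either a rank ANCOVA on one value per subject with group, age and gender, or a repeated-measures model with a group-by-visit term from which the Week 24 contrast is taken. Both answer the stated question.
- Make the Week 12 and by-period analyses secondary, and say whether a period means a successive interval or a cumulative change from baseline.
- Check that Section 8.4.3, which refers back to the primary analysis, still reads correctly.

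The change is to wording only. Scans at Study Day 1, Week 12 and Week 24 are already planned, so no data are added. The cost is some power if the effect is equal in both periods: in the illustration, 82% in place of 91%.

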### Study Subjects

It is estimated that fifty five subjects with RRMS will be screened, to achieve twenty-five intent to treat (ITT) subjects. In addition, 15 HC subjects will be enrolled as a reference group according to the same age range requirements and the same ratio of males to females as the RRMS subjects. It is estimated that the 40 subjects (25 RRMS and 15 HC) will be recruited at one center in the USA.

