## Discussion of Trial Design

This is a twenty-four week, two arm, pilot trial to evaluate remyelination, neurodegeneration (brain atrophy), iron deposition in the CNS and immune status with RRMS patients treated with Rebif® 44 mcg sc tiw compared to a HC reference group.

Subjects who sign an institutional review board (IRB) approved Subject Information Sheet and Informed Consent Form will be enrolled with a scheduled study duration of twenty-four weeks plus a four-week, post-treatment telephone call to evaluate the safety and well-being of the study subjects.

During treatment, RRMS subjects will receive Rebif® 44 mcg sc tiw. MRI measurements for RRMS and HC subjects will be performed at Study Day 1, Week 12 and Week 24/Exit.

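### The RRMS-vs-HC rank ANCOVA takes two records per subject but lists no subject term, so the 5% test has 5% size only if those records are uncorrelated

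*Protocol*

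**What the plan says.** Section 8.4.2 (Analysis of Primary Endpoint(s)) names the between-group test as "an analysis of covariance (ANCOVA) on the ranked data" and lists its terms: "with effects for treatment group (RRMS vs. HC), treatment period (1st 3 months vs. 2nd 3 months), age, and gender will be performed". The synopsis, under statistical methods, gives the same model: "ANCOVA) on the ranked data with effects for treatment group (RRMS vs. HC), treatment period (1st 3 months vs. 2nd 3 months". Neither place lists a subject effect, a repeated-measures structure or a clustered variance. The assumptions that 8.4.2 says will be verified are linearity, normality and homoscedasticity; independence of records is not among them.

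The response in 8.4.2 is "the per-voxel remyelination/demyelination count changes in NABT at 12 and 24 weeks". Section 5.1.2 defines the primary endpoint differently, as a change "from baseline to six-months in NABT of RRMS subjects treated with Rebif® as compared to NABT of HC". On scanning, section 5.2 says "MRI measurements for RRMS and HC subjects will be performed at Study Day 1, Week 12 and Week 24/Exit". On numbers, section 5.1.4 says "It is estimated that the 40 subjects (25 RRMS and 15 HC) will be recruited at one center in the USA". The test level is set in 8.4.1: "All statistical tests will be two-tailed and considered significant at an α=0.05 level of significance".

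**The concern.** Each person has one group label for the whole study, so 40 subjects supply 40 independent pieces of information about the group difference. A period effect with two levels can be estimated only if subjects contribute a record for each period, which gives 80 rows. With only group, period, age and gender in the model, the error term treats the two rows from one person as if they came from two people.

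This is the only between-group test that the protocol names for its primary endpoint, and significance is to be declared at 0.05. Section 8.4.3 has the secondary endpoints analysed similarly. If the two records are positively correlated, differences between patients and controls will be declared too often. One of the trial's stated purposes is to inform the design of later trials, so a false signal would carry forward.

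**Working it through.** The protocol states no power, effect size or standard deviation. The only stated figure to check is the 5% level.

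**Inputs.** Two-sided alpha 0.05 (8.4.1); 25 RRMS and 15 HC (5.1.4); three scans per subject, so two records each (5.2 and 8.4.2); terms group, period, age and gender (8.4.2). The within-subject correlation rho is not given and is an assumption throughout. Complete data are assumed.

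**Degrees of freedom.** As listed: 80 rows − 5 parameters (intercept, group, period, age, gender) = 75. One row per subject: 40 − 4 = 36.

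**Size of the group test.** Write s² for the variance of one record.
- The mean of a subject's two records has true variance s²(1 + rho)/2.
- The listed model takes it as s²/2.
- The between-group multiplier, 1/25 + 1/15, is the same in both and cancels.
- So true SE / model SE = sqrt(1 + rho), and actual size = 2 × [1 − Φ(1.96 / sqrt(1 + rho))].

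The formula was checked by simulation under no group difference: 25 vs 15 subjects, two log-normal records each, pooled ranks, ordinary least squares on the listed terms, 6,000 runs per value of rho.

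| Assumed rho | SE ratio | Size, formula | Size, simulated |
|---|---|---|---|
| −0.3 | 0.837 | 1.9% | 1.9% |
| 0 | 1.000 | 5.0% | 5.2% |
| 0.2 | 1.095 | 7.4% | 7.2% |
| 0.3 | 1.140 | 8.6% | 8.6% |
| 0.5 | 1.225 | 11.0% | 11.0% |
| 0.7 | 1.304 | 13.3% | 13.9% |
| 0.8 | 1.342 | 14.4% | 14.4% |

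**One row per subject.** In the same simulations, averaging each subject's two ranks gave 4.7% to 5.3%. Ranking only the Week 24 record gave 4.5% to 5.7%. That last test does not depend on rho, so its seven results estimate one quantity; their mean is (4.65 + 4.95 + 5.43 + 5.02 + 5.13 + 5.73 + 4.53)/7 = 5.1%.

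**Which sign rho takes.** Section 8.4.2 can be read two ways: both records are changes from baseline (at 12 and at 24 weeks), or they are consecutive changes (first and second three months). A three-scan model was run with independent error at each scan, a subject-specific rate of change and signed changes (4,000 runs per setting). The between-subject variance was set at 0 to 4 times the scan-error variance.
- Changes from a shared baseline: rho 0.50 to 0.86, size 11.6% to 15.6%.
- Consecutive changes sharing the Week 12 scan: rho −0.50 to 0.50, size 0.9% to 11.8%.

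In the second case the Week 12 error enters the two changes with opposite sign, which is how a negative correlation can arise.

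**Match to the endpoint.** Section 5.1.2 needs one value per subject for each direction of change, from baseline to six months. A group effect averaged over two periods estimates something else, and no period factor is needed to test the defined endpoint.

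**The case against.** **Direction.** A reader might infer that the standard error is simply too small and the p-values anti-conservative. The documents do not support that without a condition: no correlation is given, and the label of first versus second three months, read literally, means consecutive changes, for which rho could be zero or negative. This stands, and the direction must be stated as conditional. There is still reason to expect a positive value. The endpoint is a volume of voxels classed as changing, which is never negative. Stable subject traits, or a noisy Week 12 scan that adds false increases and false decreases to both intervals, would push the two records the same way. The signed-change model above leaves out that noise mechanism.

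**The SAP.** Covariance structure is often left to an SAP, and 8.4.3 defers further details to one. That a subject term is absent is inferred from the list of effects. But the protocol names the primary model and its terms itself, in two places, and the deferral sentence sits under the secondary endpoints. An SAP that added a subject term would be correcting the listed model.

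**Stakes.** It would be too strong to call this a confirmatory test. The trial is a non-randomised pilot with a healthy reference group, an aim to characterise, and a sample size not set on statistical grounds. That lowers the stakes but does not make the stated 5% level correct.

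**Reach.** A reader might take 8.4.3 to carry the fault to every secondary endpoint. It does not. Immunology is sampled at Week 24 in RRMS subjects only, the lesion-volume objective concerns RRMS subjects only, and time to first relapse is not a two-period measure.

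**The period effect.** With positive rho the listed model's period test would be too conservative. This matters little: the comparison across time within RRMS uses the Wilcoxon signed rank test, which is paired, and no endpoint is a pooled period contrast.

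**Conclusion.** The point holds in conditional form. As listed, the model takes 80 rows from 40 subjects, has no term for the subject, and tests group on 75 degrees of freedom where one row per subject would leave 36. Its size is 5% only at rho = 0. Under assumed rho of 0.2 to 0.8 the size is about 7% to 14%; at −0.3 it is about 2%. Positive correlation is likely for these volumes, most clearly if both records are changes from baseline, but that is a judgement and the protocol does not settle it. Separately, and whatever the value of rho, the model does not match the single baseline-to-six-month change that defines the primary endpoint, and the interval of the second record is unclear.

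**What to change.** In 8.4.2 and in the synopsis, define the primary group test as an ANCOVA on the ranked baseline-to-Week-24 volume, one row per subject, with group, age and gender, run separately for increasing and decreasing voxels.

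If a two-period model is kept as supportive, add a random subject effect or a repeated-measures covariance with small-sample degrees of freedom, and state which intervals the two periods cover. A GEE with uncorrected sandwich errors is not enough with 40 clusters: in simulation its size was about 7% to 8.5% across rho from −0.3 to 0.7.

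In 8.4.3, apply the same correction to those secondary MRI endpoints that are compared between groups at both visits.

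The cost is protocol wording and a small change to the model code. P-values for the group difference may become less favourable.

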### Analysis of Secondary Endpoint(s)

Secondary endpoints will be summarized at Baseline (if available), Week 12 and Week 24/Exit, using the same descriptive statistics used to analyze the primary endpoint as described above. Testing differences between groups and across time will be analyzed similarly to the primary endpoint.

Further details will be provided in a separate Statistical Analysis Plan (SAP), which will be finalized prior to performing any analyses.

